### Intervention description : control group

#### Additional lectures

The training of cardiac auscultation in the control group will be done by the conventional method (association of lectures and a clinical internship). As in the intervention group, participants will also attend three additional lectures on anatomical and physiological bases of the heart, cardiac semiology and cardiac auscultation respectively. These courses will take place at the HIMT and will be delivered in two sessions: the first course (first session) will take place on the same day as the recruitment of participants, the second and third course (second session) will take place two or three days after the first. Each course will be administered using PowerPoint presentation software and will have a duration of one hour (30 min of teaching and 30 min of question-and-answer session). These are courses given in addition to the normal theoretical training program corresponding to the normal 4th year medical studies program. These courses are delivered in addition to the normal theoretical training program corresponding to 4th year medical studies.

#### Clinical internship

Participants in the control group will be required to participate in their official clinical internship (internal medicine) also as planned by their training school. This internship will take place in all the hospitals in Yaoundé that are accredited by the HIMT and will start after the delivery of additional lectures, over a period of two months.

### Evaluation of knowledge and skills

Two evaluations (pre-test and post-test) will be organized during this study in the two groups. Each assessment will consist of two parts: a knowledge (theoretical) assessment based on multiple-choice questions and a skills (practical) assessment based on a test to recognize cardiac sounds from the audio files.

The first evaluation (pre-test, see additional file 1) will take place at the beginning of the study, directly after the recruitment of participants. The knowledge (theoretical) assessment will aim to evaluate participants’ basic knowledge and will be made on the basis of a form consisting of 15 multiple-choice questions (1 point per correct answer) validated by a scientific committee. These questions will focus on the basic anatomy and physiology of the heart, as well as the technique and semiological aspects of cardiac auscultation. The skills (practical) assessment will aim to assess the participants’ ability to recognize characteristics of cardiac sounds from audio recordings. Information on the locations of cardiac sound recording sites will be provided to participants. Participants will be invited to listen to these cardiac sound recordings using a computer connected to a loudspeaker. The five digital audio recordings selected (one normal and four pathological) will be numbered from 1 to 5. The reading sequence will be random (using a randomization tool). Each recording will be played and listened for one minute and two additional minutes will be allowed for reflection on each recording and for writing the response. Dimensions assessed will be the normal or pathological nature of a cardiac sound, timing and description of the abnormality if it is present. Each correct answer will give one point, for a total of five points.

The second evaluation (post-test, see additional file 2) will take place at the end of the participants’ clinical internships, about 60 days after the first. The purpose of this evaluation will be to measure the participants’ progress in terms of knowledge and skills according to their respective learning methods. It will also consist of a series of 20 questions similar to those in the pre-test (15 multiple-choice questions and 5 cardiac sound recognition questions). However, the questions will have a different order in the post-test form and will be defined by drawing of lots. Each question will receive an identifier based on a numeric code ranging from 1 to 15 for multiple-choice questions and from 16 to 20 for cardiac sound recognition questions. Every code will be written on paper and placed in two different ballot boxes. A person independent of the research team will be invited to randomly draw fifteen questions from the first box and fives questions from the second one.

Participant satisfaction (see additional file 3 for the control group and additional file 4 for the intervention group) will be assessed using a form containing questions whose answers will be presented in the form of a four-model Likert scale. The dimensions evaluated will be as follows: the training tools used, the pedagogy implemented and the benefits obtained by participants according to their learning methods.

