#### Listening sessions based on digital recordings of heart sounds

##### Preparation of the material

Five (5) digital audio recordings from real patients will be selected from a cardiac auscultation database designed in Cameroon in 2017 [15]. These recordings were made using a Littmann© 3200 electronic stethoscope and the resulting audio files were annotated using Audacity © software under the supervision of a cardiologist and then stored on a computer in WAV format.

Each recording corresponds to a specific cardiac sound and lasts for one (1) minute; the target cardiac sounds are as follows: heart sounds B1 and B2, aortic stenosis murmur, third heart sound (B3), fine crackles of heart failure and atrial fibrillation murmur. The selected recordings will be stored on a computer.

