##### Listening sessions

Two listening sessions of these digital recordings will be held in an FMBS classroom. Each session will be held for one hour. Each session will be organized in 3 parts: 10 min for the introduction of the activity and the presentation of tools; 40 min for listening during which each participant will have access to the 5 selected digital audio recordings of heart sounds and 10 min for feedback (collection of participants’ opinions and impressions). These recordings will be played back in a loop (series of 5) to the participants using a computer connected to loudspeakers and the Audacity© software. Four series of 10 min will be made. During these series, each recording will be broadcast for 2 min, for a total of 10 min per serie. The first series will be commented by the supervisor to help participants to identify auscultatory anomalies.

A multimedia package containing the additional lectures and the 5 digital audio recordings will be designed and made available to each participant in the intervention group at the end of the second listening session. Participants will be recommended to use this support to independently conduct similar listening sessions as often as they wish. SMS reminders will be sent to participants to encourage them to use this support.

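### As the text reads, the skills test reuses the five recordings taught only to the intervention arm, so recall and skill are confounded in skills progression and in 5 of the 20 total points

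*Protocol article*

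**What the plan says.** All references are to the protocol article.

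- **Training material** (Preparation of the material): "Five (5) digital audio recordings from real patients will be selected from a cardiac auscultation database designed in Cameroon in 2017". The target sounds are "heart sounds B1 and B2, aortic stenosis murmur, third heart sound (B3), fine crackles of heart failure and atrial fibrillation murmur". On length: "Each recording corresponds to a specific cardiac sound and lasts for one (1) minute".
- **Training** (Listening sessions): there are two sessions, in which "each participant will have access to the 5 selected digital audio recordings of heart sounds". Within a session, "Four series of 10 min will be made. During these series, each recording will be broadcast for 2 min". The supervisor comments on the first series. After the second session, intervention students receive a package with the lectures and the five recordings, and SMS messages encourage them to use it.
- **Test** (Evaluation of knowledge and skills): "The five digital audio recordings selected (one normal and four pathological) will be numbered from 1 to 5". Each is played for one minute, and the five sound items carry one point each.
- **Post-test** (same section): its questions are described as similar to those of the pre-test, but "the questions will have a different order in the post-test form". The sound items have codes 16 to 20, and five are drawn from their box.
- **Outcomes**: knowledge progression is primary. Skills progression and total progression are secondary. The section on non-adherence and missing data, however, describes the primary outcome as total progression.

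**The concern.** One arm appears to be taught, with commentary, the very items on which both arms are then scored. A student who remembers what was said about a file can earn the point without being able to identify the same sound in another patient. The control arm has no such opportunity.

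Subtracting the pre-test score does not help. The pre-test precedes training in both arms, so whatever recall the training creates enters the post-test score in full and stays in the difference.

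Skills progression is secondary, but it is the only outcome that measures sound recognition on its own. The abstract's objective names auscultation skills, the primary objective speaks of auscultation performance, and the Discussion looks to better skills among health professionals. Transfer to new patients is what those aims require, and no unheard recording is planned to measure it.

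**Working it through.** **1. Are training clips and test clips the same?**

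| Feature | Preparation of the material / Listening sessions | Evaluation of knowledge and skills |
|---|---|---|
| Number | five | five |
| Split | B1 and B2 (normal) plus four abnormal sounds | one normal, four pathological |
| Length | one minute each | played for one minute each |
| Description | the selected recordings | the recordings selected |

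The article describes no separate choice of test recordings, and nothing keeps test clips out of the sessions or the package.

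**2. Does the post-test change the clips?** The sound box holds codes 16 to 20, which is five items, and five are drawn. The number of possible sets is C(5,5) = 1, so the same five return with probability 1. Only their order can differ.

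**3. Exposure per clip outside the tests.**
- Intervention, supervised: 2 sessions × 4 series × 2 min = 16 min.
- Of this, commented: 2 sessions × 1 series × 2 min = 4 min, taking the first series of each session as commented.
- Intervention, at home: voluntary and not measured. By the Participant timeline, the second session falls about 1 + 2 = 3 weeks into an eight-week internship, which leaves about 5 weeks.
- Control: 0 min.

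Both arms also hear each clip for one minute at the pre-test, so before the post-test the supervised totals are 17 and 1 min.

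**4. Share of each score resting on these clips.** Skills: 5/5 = 100%. Total: 5/20 = 25%. Knowledge (15 multiple-choice questions): none.

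**5. Size of a possible artefact.** If recall alone raises the share of clips answered correctly by r in the intervention arm, skills progression rises by 5r points and total progression by the same number of points out of 20. The document gives no value for r. For assumed values: r = 0.10 gives 0.5 points, r = 0.20 gives 1 point, r = 0.30 gives 1.5 points.

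**6. Would such an artefact be declared significant?** This uses the plan's minimum of 23 per arm. That figure is reproduced by a two-sided 5% comparison of 80% (30 + 50) with 40% (30 + 10) at 80% power without continuity correction: 23 per arm, 46 in all. It was set on knowledge.

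With no transferable gain, a mean recall advantage of δ points and standard deviation σ of the progression score, the probability of a significant difference is approximately Φ(δ / (σ√(2/23)) − 1.96). For δ = 1 and σ = 1: √(2/23) = 0.295, 1/0.295 = 3.39, 3.39 − 1.96 = 1.43, so the probability is 0.92. The document gives no standard deviations, so all of those below are assumptions.

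| Extra clips recalled (δ) | Skills, SD 1.0 | Skills, SD 1.25 | Skills, SD 1.5 | Total, SD 2 | Total, SD 3 |
|---|---|---|---|---|---|
| 0.5 | 0.40 | 0.27 | 0.20 | 0.13 | 0.08 |
| 1 | 0.92 | 0.77 | 0.62 | 0.40 | 0.20 |
| 2 | 1.00 | 1.00 | 0.995 | 0.92 | 0.62 |

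These figures show how sensitive the outcomes would be to recall. They do not estimate how much recall will occur.

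**The case against.** **The identity of the clips is not stated outright.** No sentence says that the test uses the training recordings, the post-test questions are called similar rather than identical, and additional files 1 and 2, which hold the forms, are not shown. This stands as a limit on certainty. It does not remove the point: every described feature matches, no other source of test clips is given, and if separate clips were intended the text needs to say so.

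**A reader might infer that the test measures memory instead of skill.** The document does not support that. The test asks whether the sound is normal, its timing and a description of the abnormality, and training on a clip may teach something real. The two are confounded; skill is not shown to be absent. Nor is total progression a measure of memory, since 15 of its 20 points do not involve the clips.

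**A reader might also infer that the primary outcome is compromised.** Under Outcomes, Table 1, the abstract and Sample size, the primary outcome is knowledge, which uses no recordings. Only the sentence in the missing-data section, which equates the primary outcome with total progression, would carry the problem into it.

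**Exposure should not be overstated.** One series in four is commented, home use is optional, and the package arrives only after the second session. That is correct, and it limits how much recall can be presumed. The contrast in supervised exposure, 16 against 0 min per clip, remains.

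**Conclusion.** The point holds for two secondary outcomes. On the text, the recordings in both skills tests are the ones played to the intervention arm and given to it to keep, and the post-test draw cannot change the set. Skills progression then cannot separate recall of five files from recognition of those sounds in a new patient, and the bias runs towards the intervention. The same applies to 5 of the 20 points of total progression.

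The size of the bias is unknown. It is one skills point for each extra clip recalled, and at 23 per arm an average of one clip would produce a significant skills result with probability 0.62 to 0.92 under assumed standard deviations of 1.5 to 1.0. A larger sample would not cure this.

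The conclusion rests on the inference that training and test clips are identical, which the test forms could confirm or refute. The primary outcome as defined under Outcomes is untouched. That section and the missing-data section disagree on what the primary outcome is and must be reconciled.

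**What to change.** 1. State which recordings the pre-test and post-test use.
2. For the post-test, and preferably the pre-test, use recordings of the same five sound types from other patients in the existing annotated database, as far as it holds them. Keep them out of the listening sessions and the multimedia package. If the pre-test and post-test sets differ in difficulty, both arms face the same difference.
3. If trained clips are kept, report their score separately as recall, and do not interpret it as transferable auscultation skill.
4. Make the missing-data section and the Outcomes section agree on the primary outcome.

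Cost: up to ten further clips (five per test) to select and validate, revised test forms, and an amendment to the ethics committee and the registry. The article gives neither the size nor the contents of the database, so availability must be checked first. The sample size does not change, because it was set on knowledge. The observed skills effect will probably be smaller.

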### Criteria for discontinuing or modifying allocated interventions

This study compares a classic approach to training auscultation students versus a hybrid method which combines listening sessions based on recorded digital heart sounds. It does not involve the administration of drugs that may cause harms or worsening disease. There is therefore no reason to justify the discontinuity or the modification of the intervention for a participant.

### Strategies to improve adherence to interventions

 Strategies to improve adherence to intervention protocols will be based on the use of a tracking sheet containing the phone numbers of each participant, on phone calls made by investigators regularly to invite participants to sessions and to follow up them and on visits (supervision) of their clinical internships. Listening sessions and evaluation will be planned according to the participants’ academic schedules.

### Relevant concomitant care permitted or prohibited during the trial

Participants will be allowed to access all teaching materials in accordance with their learning processes as defined by their respective training schools.

### Provisions for post-trial care

 The study is based on a non-invasive intervention for the participants (lectures, clinical internships, listening sessions). The risks incurred during the process (namely during the clinical internships) will be covered respectively by the participants’ training schools and the accredited hospitals.

### Outcomes

Baseline data will consist of presenting the socio-demographic data of the learners, the pre-test knowledge score, the pre-test skills score, the pre-test total score, the post-test knowledge score, the post-test skills score and the post-test total score.

The primary outcome will be the progression of participants’ knowledge in cardiac auscultation. It will be evaluated on the basis of the difference between the participants’ knowledge score in the post-test and the participants’ knowledge score in the pre-test.

The secondary outcome will be: (i) the progression of participants’ skills in cardiac auscultation (based on the difference between the participants’ skill score in the post-test and the participants’ skill score in the pre-test), (ii) the total progression of participants’ knowledge and skills in cardiac auscultation (based on the difference between the total score obtained by the participants in the post-test and the total score obtained in the pre-test) and (iii) the participants’ satisfaction (Table 1).

**Table 1 Tab1:** Outcomes

Outcomes	Measurement	Type	Statistical analysis
**Primary outcome**			
Progression of participants’ knowledge in cardiac auscultation.	Difference between knowledge post and pre-test score	Continue	t-test or non-parametric equivalent
**Secondary outcomes**			
Progression of participants’ skills^a^ in cardiac auscultation	Difference between skills^a^ post and pre-test score	Continue	t-test or non-parametric equivalent
Total progression of participants’ knowledge and skills^a^ in cardiac auscultation	Difference between total progression post and pre-test score	Continue	t-test or non-parametric equivalent
Satisfaction	Satisfaction score	Ordinal	Non parametric test

^a^Recognition of cardiac sounds

### Participant timeline

For all groups, enrolment, allocation of participants and pre-test will take place simultaneously at the beginning of the study. Thereafter, the additional lectures will be given one week before the beginning of the clinical internship. The clinical internship will be held over a period of eight weeks.

For intervention group, the first listening session will take place one week after the beginning of the clinical internship, while the second listening is held two weeks after the first session. The post-test will take place at the end of the clinical internship (Fig. 2).

**Fig. 2 Fig2:**
[figure not shown]
Participant timeline. **t_0_: beginning of the study; t_1_: first week of clinical internship; t_2_: second week of clinical internship; t_3_: fourth week of clinical internship; t_4_: end of clinical internship (eighth week); t_5_: end of the study (close-out)

### Sample size

The minimum sample size will be calculated on the basis of a comparison of the average knowledge progression between the two groups. The hypothesis is that participants in the intervention and control groups will have an average of 30 % correct answers in the pre-tests and a 50 % increase in the intervention group compared to 10 % in the control group in the post-tests, i.e., an expected difference of 40 % between the two groups. For a power of 80 %, a ratio of 1:1 per group and an alpha error of 5 %, the minimum sample size will be 46 participants (23 per arm) [16]. Given the high risk of a refusal to participate, absenteeism and loss of sight, the minimum sample size will be increased by 20 %, for a total of 56 participants.

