Patient simulators aims to facilitate learning of auscultation while overcoming some of the limitations of bedside teaching (variability of symptoms, high student-patient ratios, etc.) [18, 30]. This learning method is based on the use of a life-size manikin capable of generating synthetic cardiac sounds [12, 18, 20]. Patient simulators can improve the knowledge and skills of the learners (up to 30 %) by allowing them to listen repeatedly to cardiac sounds in conditions similar to those of the clinical environment [12, 18, 20, 31]. However, it does not allow an autonomous learning of auscultation (the manikin is often kept in the faculty). Specialized software aims to improve auscultation skills by reflecting the examination process of patients and developing learners’ integration of eyes and ears findings [19, 24, 25, 32]. This method consists of real patient’s examination filmed at the bedside, coupled with recorded cardiopulmonary sound [12, 32, 33]. Depending on the software used, a progression up to 70 % of the learners’ knowledge and skills can be observed [24, 25]. Mobile application and computer-based independent learning methods aim to facilitate the acquisition of auscultation knowledge and skills, while preserving the learner’s autonomy [14, 28, 34, 35]. It is based on the use of mobile applications or multimedia supports (CDs) which allow access to cardiopulmonary sounds and lectures [36]. The effects of this method on the knowledge of the learners are similar to those of lectures [8, 12]. However, the use of this method can reduce the teaching burden in medical schools when compared with conventional lectures [12, 29, 35]. The electronic stethoscope is often associated with software to visualize the phonograph [37]. It offers the possibility to record cardiopulmonary sounds of real patients that can be shared with one or more students or used as a teaching tool for other learning methods based on listening to audio files [37]. Moreover, the use of an electronic stethoscope instead of a traditional stethoscope during clinical internships can improve learners’ skills (up to 51.2 %) [38–40].

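### The 23 per arm is reproduced by a two-proportion formula (80% vs 40%), not by the planned comparison of mean progression, so the stated 80% power is not that of the primary analysis

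*Protocol article*

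**What the plan says.** The Sample size section says the number was "calculated on the basis of a comparison of the average knowledge progression between the two groups". Its inputs are all percentages:

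- "an average of 30 % correct answers in the pre-tests" in both groups;
- "a 50 % increase in the intervention group compared to 10 % in the control group in the post-tests";
- "an expected difference of 40 % between the two groups".

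With 80% power, 1:1 allocation and 5% alpha (sidedness not stated), it concludes that "the minimum sample size will be 46 participants (23 per arm"), and adds 20% to reach 56. It gives no SD and no standardised effect. It names no formula, only a citation, and the cited source was not available for this check.

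The Outcomes section defines the primary outcome as each student's post-test knowledge score minus the pre-test score. The test has 15 questions at one mark each (Evaluation of knowledge and skills). Table 1 classes the outcome as continuous and gives its analysis as "t-test or non-parametric equivalent". The Statistical methods section says the same. No pass mark or other binary knowledge endpoint is defined.

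**The concern.** A sample size for comparing two means needs the difference and the SD of what is averaged. Here the SD is the quantity that decides the answer, and it is absent. A sample size for comparing two proportions needs only the two percentages, because they fix the variance. The section announces the first kind of calculation but supplies inputs only for the second.

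The two are not interchangeable. A two-proportion formula gives each student the variance of a single right-or-wrong answer. A student's score averages 15 answers and varies far less. If the formula was applied to percentage scores, the 80% power describes a test that nobody will run. This calculation is the only justification given for the trial's size, and from it a reader cannot tell what difference in marks the trial is able to detect.

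**Working it through.** **1. Reproduce the stated figure.** Reading the increases as percentage points, the post-test levels are 30 + 50 = 80% and 30 + 10 = 40%. Take two-sided alpha 5% (z = 1.960), power 80% (z = 0.842) and mean proportion 0.60:

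n = [1.960 × √(2 × 0.60 × 0.40) + 0.842 × √(0.80 × 0.20 + 0.40 × 0.60)]² / 0.40²

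= [1.960 × 0.6928 + 0.842 × 0.6325]² / 0.16 = 22.33, rounded up to **23 per arm, 46 in total**. This matches the protocol exactly. The power of that test at 23 per arm is 81.2%.

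Other variants for 80% vs 40%, per arm:

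- two-sided with continuity correction: 28
- two-sided, unpooled variance: 20
- two-sided, arcsine: 22
- one-sided: 18
- one-sided with continuity correction: 23

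The only other variant here that gives 23 is still a two-proportion formula.

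**2. Try the announced calculation.** For two means, n = 2 × (1.960 + 0.842)² × SD² / 40². This cannot be evaluated from the document because the SD is missing. Working backwards, an SD of 47 points gives 22 per arm, 48 gives 23 and 49 gives 24. With the t distribution, 23 per arm has 80% power at a standardised difference of 0.845, so the implied SD is 40 / 0.845 = **47.4 points**, or 0.474 × 15 = **7.1 marks**.

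**3. Compare with what a 15-item test can be expected to give.** Binomial error alone, from a pre-test at 30% and a post-test at 80% or 40%, gives a change-score SD of:

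- intervention: √[(0.30 × 0.70 + 0.80 × 0.20) / 15] = √(0.37 / 15) = 15.7 points
- control: √[(0.30 × 0.70 + 0.40 × 0.60) / 15] = √(0.45 / 15) = 17.3 points

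That is about 16 to 17 points. Real differences between students in how much they gain add to this, so 17 to 30 points is taken as an assumed working range.

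**4. Power of the t-test with 23 per arm for a 40-point difference.**

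| Assumed SD (points) | Power |
|---|---|
| 20 | >99% |
| 30 | 99.3% |
| 40 | 91.2% |
| 47 | 80.6% |
| 50 | 75.6% |
| 60 | 59.9% |

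By the normal approximation, 80% power for 40 points needs 7 per arm at SD 25 and 9 per arm at SD 30.

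**5. What 23 per arm does support.** It gives 80% power for 0.845 SD. At SD 17 that is 14.4 points, or 2.2 marks. At SD 25 it is 21.1 points, or 3.2 marks.

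**The case against.** The strongest reply is that the formula is inferred. None is named, the cited source is not at hand, and a journal article may leave the SD to a fuller document. This stands as far as wording goes: one can say that 23 is reproduced by the two-proportion formula, not that it certainly came from it. But an unprinted SD would rescue the figure only if it were about 47 to 48 points, and the printed inputs are complete for one calculation and unusable for the other.

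A second reply is that nothing practical follows: on the authors' hypothesis 23 per arm is ample, and what a null result excludes is read from its confidence interval. This also stands. It limits the weight of the point but does not make the power statement correct.

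Three stronger readings are tempting and are not supported:

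- **That the trial is underpowered.** If the increases were relative, 30% would become 45% and 33%, a gap of only 12 points. But the section itself states a 40% difference, and the exact match to 23 arises only with percentage points; 45% vs 33% as proportions would need 259 per arm.
- **That an SD of 47 points is impossible.** A post-test score alone could not spread that far at these means, but the outcome is a change score and also carries pre-test variance. With all-or-nothing scoring and uncorrelated tests its SD would be √(0.16 + 0.21) = 61 points (intervention) and √(0.24 + 0.21) = 67 points (control). So 47 is implausible, not excluded.
- **That the Discussion contradicts the 40-point gap.** Its remark that "The effects of this method on the knowledge of the learners are similar to those of lectures" concerns independent mobile and computer-based learning. Here both arms receive the lectures and the intervention adds supervised listening. The same section reports progression of up to 70% with specialised software.

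The inflation is also not at fault: 46 × 1.2 = 55.2, so 56 is a 20% increase, as stated.

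**Conclusion.** The power statement is wrong as written. It is attached to a comparison of mean progression, but its inputs reproduce the stated number only as a comparison of two proportions, an analysis that is not planned for an endpoint that does not exist. For the planned t-test, 80% power at 23 per arm and 40 points requires a change-score SD of about 47 points, nearly three times the 16 to 17 points that binomial error gives. At an assumed SD of 17 to 30 points, power exceeds 99%, so on the authors' hypothesis the figure is understated.

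This rests on a two-sided 5% level, on the percentage-point reading, and on an SD range that is assumed because the document gives none. It does not show that the trial is too small. The defect lies in the justification, not in the number to be enrolled.

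**What to change.** Replace the calculation with a two-sample comparison of mean progression in marks out of 15. In that paragraph:

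- say that the 50% and 10% increases are percentage points, so the hypothesised difference is 40 points, or 6 of 15 marks (0.40 × 15);
- give an assumed SD of the change score, with its source and a range;
- state the sidedness of the test and name the formula;
- restate the claim as: 23 per arm gives 80% power to detect a difference of 0.84 SD, about 2.2 to 3.2 marks at an assumed SD of 17 to 25 points.

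The cost is the rewording of one paragraph. The 46 evaluable and 56 enrolled participants, the outcome and the analysis can all stay as they are.
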